### Measures

#### Primary outcome

#### Units consumed per week - daily drinking questionnaire

The primary outcome is alcohol consumption in units per week assessed via the Daily Drinking Questionnaire [13]. The measure asks students for details of a typical week rather than exact quantities for the last 7 days, in order to ensure that it reflects habitual drinking. The DDQ has emerged as a favoured measure within RCTs with students due to its brevity, its convergent validity with more laborious drinking measures [13], acceptable internal consistency (Neighbors et al. 2002), good 2-month test-retest reliability for volume and adequate test-retest reliability for frequency [14]) and established ability to detect post-intervention changes. Importantly, the measure also provides comparable estimates regardless of whether administered via the internet or as a pen and paper exercise [15]

### Secondary outcomes

#### Weekly alcohol consumption behaviours - daily drinking questionnaire

Responses can also provide a measure of i) number of days per week drinking in a typical week, ii) number of units per sitting and iv) number of heavy drinking episodes per week.

#### [***Prevalence of higher risk drinking - AUDIT***

The consumption subscale of the Alcohol Use Disorders Identification Tool (AUDIT p15;[16] provides an additional measure of alcohol consumption, allowing estimation of the prevalence of potentially hazardous drinking in control/intervention halls. The scale includes items on frequency of drinking, volume per drinking occasion and frequency of 'binge drinking' (e.g. 8+/6+ units on one occasion for men/women), each scored on a scale of 0-4. In primary care studies, a total summed score of 4 or above for men, or 3 or above for women, has been shown to optimally identify potentially hazardous drinkers [17]

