## Background

Excessive alcohol consumption among university students has been linked to a range of adverse outcomes, including educational difficulties, psychosocial problems, antisocial behaviours, injuries, risky sexual behaviours and drink driving [1]. In the United Kingdom, alcohol consumption levels amongst university aged adults increased rapidly during the 1990s [2]. Recent studies suggest that just over half of UK university students 'binge drink' (i.e. consume 5 or more drinks in one sitting) at least once per week [3,4], whilst as many as 80% binge drink at least once a month [4]. One recent study estimated average alcohol consumption at 25 units per week for 1^st ^year male UK undergraduates and 16 for 1st year women [5], significantly above current public health recommendations. Recent UK government policy of increasing the percentage of young people going to university has perhaps had the effect of exposing a larger proportion of the population to this high-risk drinking environment.

Alcohol consumption amongst university students has to date proved highly resistant to intervention efforts [6]. One approach, which has shown some promise in experimental studies, is addressing the perceived social norms that are posited to influence alcohol consumption [7]. Perceived norms take the form of descriptive norms, with behaviour modelled through observation of the behaviour of significant others; or injunctive norms, where the individual perceives that their peers expect them to behave a certain way. Interventions underpinned by the social norms approach argue that normative perceptions are highly fallible, with students often overestimating real alcohol consumption patterns among peers [8]. Hence, through providing feedback and correcting misperceptions regarding the behaviours and social expectations of peers, alcohol drinking behaviours may be reduced. Social norms interventions have typically involved provision of mailed, web-based or face-to-face feedback on individual's drinking behaviour and how this compares to norms for their peer group, or social marketing campaigns to promote awareness of actual norms. A recent Cochrane review concluded that feedback-based interventions delivered via the internet or face-to-face on a one-to-one basis appeared to reduce student drinking behaviours, though mailed or group feedback were less effective, and findings for social marketing campaigns were equivocal [7].

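### The only AUDIT outcome the protocol defines is a prevalence at primary-care cut-offs that most of these students probably exceed; the summed 0-12 score should be analysed as well

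*Protocol article*

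**What the plan says.** The protocol article's Secondary outcomes section has an entry on higher-risk drinking, titled as a prevalence. It says that the AUDIT consumption subscale "provides an additional measure of alcohol consumption, allowing estimation of the prevalence of potentially hazardous drinking in control/intervention halls". The subscale has three items (frequency, volume per occasion, frequency of binge drinking), "each scored on a scale of 0-4", so the total runs from 0 to 12. The only cut-offs named, which the entry attributes to primary care studies, are "a total summed score of 4 or above for men, or 3 or above for women".

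The next entry, on the Rutgers index, states that its items are typically summed into one continuous variable. The AUDIT entry has no matching statement; the summed score appears only as the quantity to which the cut-off applies.

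The Background describes the target population. It opens "Recent studies suggest that just over half of UK university students" and goes on to say that these students binge drink at least weekly, "whilst as many as 80% binge drink at least once a month". It also cites a study that put "average alcohol consumption at 25 units per week for 1^st ^year male UK undergraduates and 16 for 1st year women".

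The Analysis section names no AUDIT analysis. Its regression, with a random hall term and fixed stratification terms, is specified for normative perceptions and alcohol related consequences. Intra-cluster correlations and SDs are promised for units per week.

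**The concern.** Cut-offs of 4 and 3 on a 0-12 scale lie at a third and a quarter of the maximum. They were chosen to separate hazardous from other drinkers in primary care. In a population that drinks as the Background describes, most students probably score above them. The split then falls in the lower tail of the distribution, and a student who cuts down but stays above the line counts as unchanged.

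The Research design and Discussion text gives the identification of suitable outcome measures for a definitive trial as a purpose of this study. A prevalence near its ceiling says little about how well the instrument registers a shift in drinking. If the binary outcome were carried forward, the definitive trial would need to be larger than with the score.

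**Working it through.** **Inputs from the protocol.** Sample size section: 50 halls; 1600 students (32 per hall) or 1000 (20 per hall); intra-cluster correlation (ICC) 0.03; two-sided alpha 0.05; 80% power. Allocation is 25 halls against 25.

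**Inputs assumed.** The share p above the cut-off is not given, so a range of 70-90% is used. The score is taken as roughly normal.

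**1. The plan's own figure.** Design effect = 1 + (m - 1) x ICC.
- 32 per hall: 1 + 31 x 0.03 = 1.93; effective N = 1600/1.93 = 829. Power at 0.2 SD is 82.1% (normal) or 80.5% (t, 48 df).
- 20 per hall: 1 + 19 x 0.03 = 1.57; effective N = 1000/1.57 = 637. Power at 0.23 SD is 82.7% or 81.2%.

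The stated 80% is reproduced. With 1600 students the detectable difference for a continuous score is 2.80 x sqrt(4 x 1.93/1600) = 0.195 SD.

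**2. Efficiency of the split, same ICC.** Relative efficiency = phi(z_p)^2 / [p(1 - p)], where phi is the standard normal density at the cut.
- p = 0.70: 0.348^2/0.21 = 0.576
- p = 0.80: 0.280^2/0.16 = 0.490
- p = 0.90: 0.1755^2/0.09 = 0.342

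Even a split at the median keeps only 0.637. A loss of one half is reached at p = 0.79.

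The detectable difference in prevalence is 2.80 x sqrt(p(1 - p) x 4 x 1.93/1600); dividing by phi(z_p) gives the matching shift in SD.

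| Share above cut | Information lost | Detectable difference | Equivalent shift | Power for a 0.2 SD shift |
|---|---|---|---|---|
| Score kept whole | 0% | - | 0.195 SD | 82% |
| 70% | 42% | 8.9 points | 0.26 SD | 60% |
| 80% | 51% | 7.8 points | 0.28 SD | 54% |
| 90% | 66% | 5.8 points | 0.33 SD | 42% |

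(1600 students, design effect 1.93 throughout.)

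**3. Allowing the split to lower the ICC.** The ICC of the binary outcome is approximately 0.03 x the relative efficiency. At p = 0.80 it is 0.03 x 0.490 = 0.0147. The design effect with 32 per hall becomes 1 + 31 x 0.0147 = 1.456, and the net efficiency is 0.490 x 1.93/1.456 = 0.650.

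| Share above cut | ICC of the split | Net loss, 32 per hall | Net loss, 20 per hall |
|---|---|---|---|
| 70% | 0.017 | 28% | 32% |
| 80% | 0.015 | 35% | 40% |
| 90% | 0.010 | 50% | 55% |

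On this basis a loss of one half is reached only at p of about 0.90 (32 per hall) or 0.87 (20 per hall).

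**4. Check on the discrete scale.** With a normal score rounded to 0-12 and SDs of 2, 2.5 and 3, relative efficiency at the same ICC is 0.588-0.590 (p = 0.70), 0.498-0.501 (p = 0.80) and 0.348-0.352 (p = 0.90). Treating the score as continuous does not drive the result.

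**5. At the effect the plan regards as realistic.** The Sample size section expects effects below 0.1 SD. At p = 0.80 a 0.1 SD shift moves the prevalence by about 0.1 x 0.280 = 2.8 points. Its standard error is sqrt(0.16 x 4 x 1.93/1600) = 2.8 points.

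**The case against.** A reader might infer that higher-risk drinking will be assessed solely by this split. The article does not say so. It also calls the subscale an additional measure of consumption, the cut-off sentence reports what others have found, and the Analysis section is silent on AUDIT. An article may leave a further analysis of the score to a fuller plan. What remains is narrower: the one AUDIT outcome that the article does define is a prevalence.

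The DDQ supplies units per week, drinking days, units per sitting and heavy drinking episodes per week. These cover much the same ground as the three AUDIT items without the cut-off, so a student who drinks less but stays above the AUDIT line can still register there. This stands and limits the consequence. It does not show how AUDIT itself performs.

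A reader might also infer that at least half the information is lost. That needs about 79% or more above the cut-off, and 87-90% if the split lowers the ICC. The article gives no such share. Its 80% is an upper figure for monthly binge drinking defined as five or more drinks, not the 8+/6+ units of the AUDIT item, and the item scoring bands are not given.

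Finally, the article does not say that AUDIT will be judged by whether it separates the arms, so a wrong rejection of the instrument is a possibility and not a planned step. Neither version of the outcome would reliably detect an effect below 0.1 SD. The prevalence is also a meaningful public-health quantity in its own right, which is a reason to keep it.

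**Conclusion.** The point holds in limited form and is minor. The only defined AUDIT outcome is a prevalence at cut-offs taken from primary care, and the protocol's own background makes it plausible that most students exceed them. With 70-90% above the cut, a roughly normal score and the same ICC, the split loses about 42-66% of the information; the shift detectable with 1600 students rises from 0.195 SD to 0.26-0.33 SD. At 80% above the cut, allowing for a lower ICC reduces the loss to about 35-40%. The loss is material across the assumed range, but its exact size depends on a share that the documents do not give. The importance stays low because this is one secondary outcome, the DDQ provides other continuous and count measures, and the trial is openly exploratory and acknowledged as probably underpowered for behaviour.

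**What to change.** Add to the Analysis section that the summed 0-12 AUDIT consumption score will be compared between arms by a regression with a hall random term and fixed stratification terms. This extends the model now specified for normative perceptions and alcohol related consequences. Report the SD and ICC of the score alongside those already promised for units per week, so that the definitive trial can weigh AUDIT on its merits. Keep the prevalence at 4 (men) and 3 (women) as a descriptive figure by arm.

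The cost is a sentence or two of text and one extra reported estimate. No new data are needed, because the items are already in the survey.

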#### Alcohol related consequences - Rutgers alcohol problem index

Secondary outcomes include the 18-item version of the Rutgers Alcohol Problem Index (RAPI) [18]. The index is a well validated measure of alcohol problems with well established psychometric properties among clinical and general population samples ranging from 12 to 21 years. It is commonly used among general university populations in evaluations of alcohol based interventions. All items are typically summed to provide a single continuous variable for alcohol problems, although the factor structure in the current population will be carefully checked.

#### Descriptive norms

In order to assess whether the campaign achieves the hypothesised mechanism of changing perceived descriptive norms for drinking, the evaluation requires a measure of perceived descriptive norms. The drinking norms rating form has been widely used in RCTs and cross sectional studies (Baer et al. 1991) and involves rewording the DDQ to reference others rather than self, therefore having the advantage that perceived normative behaviour is measured in exactly the same way as own behaviour.

#### Injunctive norms

Whilst most previous studies have focused on descriptive norms, many psychological models argue that injunctive norms (i.e. perceived social pressure or social approval) are equally important in shaping behaviour. A scale previously used by Neighbors et al. (2008) was therefore included.

#### Demographics

Measures of gender, age, ethnicity, international/home student status, course studied and place of residence will facilitate an examination of the representativeness of the sample, to assess comparability between groups of students assigned to receive/not receive the social norms intervention and assess potential contamination between trial arms.

#### Acceptability of objective measures

Students will also be asked to indicate whether they would be willing to provide hair samples as an objective measure of alcohol consumption, although it will be made clear that this is a hypothetical question, and that we will not be attempting this at any point in the present study. The question is simply included to evaluate the acceptability of this method among university students if we were to seek funding for a larger definitive trial using more objective measurement approaches in the future.

### Data collection

At four months after initial implementation of the intervention, measures will be collected via a survey to all 1^st ^year university students, offered in web and paper format. They will be recruited via nominated university distribution contacts, who will circulate the link to first year students via email and electronic notice boards between mid-February and the end of March 2012. At least one reminder will be emailed to students during the data collection period. On completion of the questionnaire, data will be captured and processed by a market research company, who will prepare a complete anonymised dataset for analysis. Heads of student services provided consent for the conduct of the survey and students will not be able to complete the survey without completing informed consent tick-boxes. Students will not be asked to provide any identifiable information, other than email addresses, which will be used purely for the purpose of selecting a winner for the £100 prize draw in each university, offered as an incentive for participation. Email addresses will be separated from responses to the web survey and destroyed after the prize draw.

In an attempt to boost student responses, residence hall managers will be asked to promote the survey and the prize draw to residents. To compare the efficacy of two data collection approaches, a paper copy of the questionnaire will be distributed to student halls of residence via accommodation managers, inviting students either to complete the paper copy and return it to the research team in a freepost envelope, or to go to the web-page to complete the survey online. Questionnaires completed in paper form will be returned to the research team in freepost envelopes. These will be stored in a locked cabinet until the web survey data-file is received from the survey company, at which point, questionnaires will be retrieved, data entered into the data-file, and questionnaires returned to the cabinet. Participants will be offered the opportunity to enter a prize draw, with £100 offered to one winner in each participating university by supplying a university email to be kept separately to questionnaire responses. Email addresses will be recorded on a detachable sheet at the start of the questionnaire, which will be separated from the questionnaire once received, with the email address entered into a separate spread sheet and the paper copy destroyed.

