**Methods/design:**

The study adopts an exploratory cluster randomised controlled trial design with halls of residence as the unit of allocation, and a nested mixed methods process evaluation. Four Welsh (UK) universities participated in the study, with residence hall managers consenting to implementation of the trial in 50 university owned campus based halls of residence. Consenting halls were randomised to either a phased multi channel social norm marketing campaign addressing normative discrepancies (n = 25 intervention) or normal practice (n = 25 control). The primary outcome is alcohol consumption (units per week) measured using the Daily Drinking Questionnaire. Secondary outcomes assess frequency of alcohol consumption, higher risk drinking, alcohol related problems and change in perceptions of alcohol-related descriptive and injunctive norms. Data will be collected for all 50 halls at 4 months follow up through a cross-sectional on line and postal survey of approximately 4000 first year students. The process evaluation will explore the acceptability and implementation of the social norms intervention and toolkit and hypothesised process of change including awareness, receptivity and normative changes.

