An exploratory cluster randomised design with nested process evaluation will be used to identify appropriate outcome measures and data collection methods, test randomisation processes, assess the extent of contamination across trial arms and establish recruitment and retention rates and intra-cluster correlations to help inform sample size for any future definitive trial. It will also identify whether the intervention effectively mobilises the underpinning theory and that this is sufficient to bring about hypothesised responses in terms of awareness, engagement and changed perception of norms. Whilst intervention acceptability and implementation processes will be assessed within the process evaluation.

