### Randomisation

Blind remote randomisation was used to allocate halls of residence to receive the social norms plus toolkit intervention or toolkit only. Halls were stratified by institution and halls allocated alternately in a list ordered by size, with the group allocation determined by one random number within each stratum.

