### Analysis

In order to assess exposure to intervention materials and contamination between trial arms, percentages of students within the intervention and control groups reporting having seen each of the intervention materials i) in their own hall of residence and ii) in another students' hall of residence will be examined. Among those students reporting exposure to intervention materials, percentages correctly identifying the messages within them will be calculated for each trial arm. Percentages of students reporting each level of agreement with statements regarding the credibility, relevance and perceived impacts of intervention materials will also be examined for each trial arm.

Whilst the study is likely not sufficiently powered to detect impacts on behaviour, it is likely that relatively large changes in perceived norms will be necessary to produce small changes in behaviour. Hence, regression analyses, with random terms to adjust for clustering at the hall level, and fixed terms to adjust for stratification variables, will examine differences between intervention and control participants in terms of normative perceptions for alcohol consumption and alcohol related consequences. Comparisons between trial arms will be conducted on an intention-to-treat basis. Secondary analyses would compare halls on the basis of researcher observations of whether or not materials were placed.

To inform the design of a potential large scale definitive trial with sufficient power to detect changes in behaviour, intra-cluster correlations and standard deviations will be calculated for total number of units per week. Response rates will be calculated in each trial arm. The percentage of students reporting willingness to provide hair samples will also be presented, whilst among those students reporting that they would only do so if paid, percentages reporting that each level of payment would be required would be presented.

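### With web and paper offered together in the halls, the survey can describe uptake by mode but cannot compare the modes' efficacy or show how much response paper adds

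*Protocol article*

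**What the plan says.** The Data collection section of the protocol article describes the web route first: university contacts "who will circulate the link to first year students via email and electronic notice boards" between mid-February and the end of March 2012, with at least one emailed reminder. It introduces paper with a stated purpose: "To compare the efficacy of two data collection approaches, a paper copy of the questionnaire will be distributed to student halls of residence", handed out through accommodation managers. The recipient may post the form back "or to go to the web-page to complete the survey online". The same section says that "measures will be collected via a survey to all 1^st ^year university students, offered in web and paper format", and the abstract says: "Data will be collected for all 50 halls at 4 months follow up through a cross-sectional on line and postal survey".

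The Randomisation section has one allocation only, to "allocate halls of residence to receive the social norms plus toolkit intervention or toolkit only". Survey mode is not allocated, and no staggering of the two modes is described.

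The Background section says that the design will be used to "identify appropriate outcome measures and data collection methods", and the Discussion counts cost-effective data collection among the things a definitive trial requires.

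**The concern.** Comparing the efficacy of two approaches needs a contrast: some units offered one approach and comparable units offered the other, or one approach added at a time that is not tied to anything else. The procedure described creates none among hall residents. A student who replies by web may have been prompted by the email or by the pack, and both look the same in the data. A student who replies on paper might have replied by web had no pack come.

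The product of this exploratory trial is a set of design parameters. The response assumed in the Sample size section runs from 25% to 40%, so response is a leading uncertainty. Whether packs, freepost and manual data entry gain enough extra returns to be worth their cost is a question a definitive trial will face. Who receives paper, and when, is settled in the field. A later analysis plan cannot recover a contrast that was never set up.

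**Working it through.** **The plan's own figures.** The point rests on no stated figure, but the nearby ones reproduce. About 4000 students (abstract) in 50 halls is 80 per hall. 4000 × 0.40 = 1600 returns, 32 per hall; 4000 × 0.25 = 1000 returns, 20 per hall. With ICC 0.03 the design effect is 1 + 31 × 0.03 = 1.93, the effective number per arm is 25 × 32 / 1.93 = 414.5, and power for 0.2 SD is 80.5% (noncentral t, 48 df). For 20 per hall and 0.23 SD it is 81.2%. Both agree with the stated 80%.

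**What the split of returns can show.** Let w and p be the proportions of those invited who return by web and by paper when both are on offer. Make two assumptions that favour the design: anyone who would reply to one mode offered alone also replies when both are offered, and anyone who used a mode would have used it had it been the only one. Then:

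- the web-only response lies in [w, w + p];
- the paper-only response lies in [p, w + p];
- their difference (web minus paper) lies in [-p, +w], which contains zero for every split;
- the response that paper adds to web lies in [0, p].

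The split is not known in advance; take 70% of returns by web as an assumption.

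| Total response | w | p | Web-only | Paper-only | Difference (points) | Added by paper (points) |
|---|---|---|---|---|---|---|
| 40% | 28% | 12% | 28% to 40% | 12% to 40% | -12 to +28 | 0 to 12 |
| 25% | 17.5% | 7.5% | 17.5% to 25% | 7.5% to 25% | -7.5 to +17.5 | 0 to 7.5 |

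At 40% response, a 50% web share gives -20 to +20 points and a 90% share gives -4 to +36. Even the sign is not identified. The second assumption is generous to the design: if the pack prompted some of the web returns, the web-only response can fall below w and the yield of paper can exceed p.

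**What a randomised stagger could detect.** Compare 25 with 25 halls of 80 residents, two-sided alpha 0.05, 80% power. The documents give an ICC for units of alcohol (0.03) but none for response, so a range is assumed. Design effect = 1 + 79 × ICC; effective n per group = 2000 / design effect. The detectable difference d solves d = 1.96 × √(2·p̄(1 − p̄)/n) + 0.84 × √((p₁(1 − p₁) + p₂(1 − p₂))/n), with p₂ = p₁ + d and p̄ their mean.

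| Assumed ICC of response | Design effect | Effective n | d, base 15% | d, base 25% | d, base 40% |
|---|---|---|---|---|---|
| 0.01 | 1.79 | 1117 | 4.5 | 5.3 | 5.9 |
| 0.03 | 3.37 | 593 | 6.3 | 7.4 | 8.1 |
| 0.05 | 4.95 | 404 | 7.7 | 9.0 | 9.8 |
| 0.10 | 8.90 | 225 | 10.6 | 12.2 | 13.2 |

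(d in percentage points.) The 25% and 40% bases are the plan's assumed final response rates. The 15% base is an assumption for the lower response to be expected about halfway through the window. Equal hall sizes are assumed; unequal halls would raise these figures somewhat.

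**The case against.** The best defence is that efficacy here means practical performance with both routes open. Paper forms arrive separately from the web file and demographics are collected, so the trial can report returns by mode, who used each, and forms returned per pack delivered. That stands, and it helps in costing. A reader might infer that the trial learns nothing about modes; the documents do not support that. But these are descriptions of preference. They do not tell us what response would have been without paper.

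Four other stronger readings also fail.

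- *Nobody lacks paper.* About half of first-year students live in halls (Background), and those outside apparently get only the link. They are no usable control group, because mode is then confounded with residence. That every hall gets paper is itself read from the Data collection section together with the abstract.
- *A named trial objective is defeated.* The objectives list data collection methods in general. The comparison of two approaches is a stated purpose of the paper copies in one sentence.
- *The missing analysis by mode proves the point.* The Analysis section says "Response rates will be calculated in each trial arm" and does not exclude other tabulations; such detail may sit in a fuller plan. The point rests on the delivery procedure alone.
- *The trial result is biased.* Both arms are offered both modes, so the arm comparison, the ICC and the SD are not distorted by this.

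A contrast of response before and after the packs arrive would not rescue the comparison. It would be confounded with reminders and calendar time.

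**Conclusion.** The point holds in a limited form. The stated comparison of efficacy cannot be made, because hall residents are offered both modes, the pack also leads to the web, and mode is neither randomised nor staggered. Neither the direction of the difference between modes nor the yield of paper is identified: at 40% response and an assumed 70% web share, the ranges are -12 to +28 points and 0 to 12 points, and both widen if packs prompt web returns. Uptake and user profile by mode remain available.

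The damage is to one feasibility output, not to the arm comparison. It is still worth correcting, since part of the remedy costs almost nothing. The size of what a stagger could detect depends on an ICC of response that the documents do not give, so it should be quoted as a range of roughly 5 to 13 points at a base of 25% to 40%, and somewhat less at a lower mid-window response. It would show a sizeable early gain from paper, not a small one.

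**What to change.** 1. Print a web address on the packs that differs from the emailed one, and report web returns by entry address. Cost: a second link. Some pack recipients will still use the emailed link, so this count is descriptive.
2. Randomise the timing of pack delivery by hall: half the halls early in the window, the rest about three weeks later, balanced by trial arm and institution as nearly as 25 halls per arm allows. Compare response per hall just before the second delivery, logging the date of each return. Mid-February to the end of March is about six weeks, so this fits, and every hall still gets paper. Place of residence is already collected.
3. State that this estimates the early added yield of paper, not its total over the window.

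The cost is a delivery list and dated returns. Half the halls have paper for about three weeks less, which may lose some returns, and accommodation managers must keep to two delivery dates.

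If staggering is not feasible, keep the separate address and reword the Data collection sentence to say that the study will describe uptake by mode and will not compare efficacy.
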